**Methods:**

We will conduct a 24-month, parallel, open-label, multicenter, pragmatic, hybrid type 1 randomized clinical trial. 118 primary healthcare centers with wide geographical distribution in Spain will be randomly assigned (ratio 1:1) to two groups. The intervention group will receive two audits (baseline and intermediate at 12 months) based on information collected through the administration of the PREOS-PC questionnaire (a measure of patient-reported patient safety) to a convenience sample of 100 patients per center. The intervention group will receive reports on the results of both audits, along with educational resources aimed at facilitating the design and implementation of safety improvement plans. The control group will receive care as usual. The primary outcome will be the rate of avoidable hospitalizations (administrative data). Secondary outcomes: patient-reported patient safety experiences and outcomes (PREOS-PC questionnaire); patient safety culture as perceived by professionals (MOSPSC questionnaire); adverse events reported by healthcare professionals (*ad hoc* questionnaire); the number of safety improvement actions which the re has implemented (*ad hoc* questionnaire). Outcome data will be collected at baseline and 24 months follow-up. For the evaluation of the implementation of the SinergiAPS intervention, we will draw on the Consolidated Framework for Implementation Research (CFIR). We will collect and analyze qualitative and quantitative data (30 individual interviews, implementation logbooks; questionnaires for professionals from intervention centers, and level of use of the SinergiAPS web tool).

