Burden of harm: 3 items (Cronbach’s α = 0.73) that evaluate the impact and consequences of the harm experienced by patients	Patient-reported (PREOS-PC Compact)	Practice level (mean score—theoretical range: 0 to 100)	Baseline and 24 months follow-up
Overall assessment of the center’s safety level (1 item). Visual analogue scale.	Patient-reported (PREOS-PC Compact)	Practice level (mean score—theoretical range: 0 to 100)	Baseline and 24 months follow-up
Patient safety culture	Healthcare provider-reported (MOSPSC questionnaire)	Practice level (mean score—theoretical range: 0 to 5)	Baseline and 24 months follow-up
Frequency of adverse events experienced by healthcare professionals in the last 12 months	Healthcare provider-reported (*ad hoc* questionnaire)	Practice level (mean score—theoretical range: 0 to 100)	Baseline and 24 months follow-up
Impact of adverse events on healthcare providers wellbeing	Healthcare provider-reported (*ad hoc* questionnaire)	Practice level (mean score—theoretical range: 0 to 100)	Baseline and 24 months follow-up
Number of actions aimed at improving patient safety in the center in the last 12 months	Reported by the practice responsible for patient safety	Practice level (total number)	24 months follow-up
3. Implementation and process evaluation (only centers allocated to the intervention group)			
Number of accesses to the SinergiAPS tool	Metadata from SinergiAPS tool	Practice level (total number)	Monthly during the 24 months of follow up period
Time using the SinergiAPS tool	Metadata from SinergiAPS tool	Practice level (number of minutes)	Monthly during the 24 months of follow up period
Number of safety improvement actions registered in the SinergiAPS tool	Metadata from SinergiAPS tool	Practice level (total number)	Quarterly during the 24 months of follow up period
Usage of the SinergiAPS tool	Reported by the practice responsible for patient safety (*ad hoc* questionnaire)	Practice level (number of hours)	Quarterly during the 24 months of follow up period
Perceived utility and satisfaction with the SinergiAPS tool	Reported by the practice responsible for patient safety (*ad hoc* structured questionnaire)	Practice level (mean score—theoretical range: 0 to 100)	Quarterly during the 24 months of follow up period

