#### Secondary outcome measures

2.8.2

Perceptions and experiences of patients (scores from the scales of the PREOS-PC Compact questionnaire): This questionnaire will be administered to a selected sample of 100 patients from each healthcare center. This sample size is estimated to achieve a reliability of at least 0.7 in the mean scores of the healthcare centers for the questionnaire’s scales. The questionnaire incorporates the following scales:
“Practice activation”: 4 items (Cronbach’s α = 0.71) that measure the proactivity of healthcare centers towards patient safety.“Experience of harm (severity)”: 3 items (Cronbach’s α = 0.81) that assess the level of harm suffered by patients because of the healthcare they received.“Burden of harm”: 3 items (Cronbach’s α = 0.80) that evaluate the impact and consequences of the harm experienced by patients.“Overall assessment of the center’s safety level” (1 item). Visual analogue scale.
Patient safety culture of healthcare professionals: We will calculate the average center-level score of the Patient Safety Culture Composite Score (ranging from 1–5 points), based on the responses of professionals to the Spanish version of the Medical Office Survey on Patient Safety Culture (MOSPSC) questionnaire (39).Adverse events experienced by healthcare professionals in the last 12 months: An ad hoc questionnaire will be adapted from a previous study (43) to assess the adverse events experienced by professionals (frequency and impact on healthcare professionals’ well-being).Number of actions aimed at improving patient safety in the center in the last 12 months: An ad hoc questionnaire will be administered to the quality and patient safety referent of each center, including both intervention and control centers, to determine the number of actions taken to enhance patient safety.

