#### Statistical analysis

2.8.3

Initially, we will conduct descriptive statistical analysis to characterize the participating healthcare centers. For each of the two groups (control and intervention), we will calculate frequencies (percentages) for binary or categorical variables, and medians (along with interquartile range) for continuous variables. The effectiveness of the intervention will be analyzed by comparing the mean score of the primary outcome variable (rate of avoidable hospitalizations) between the control and intervention groups after 24 months of follow-up. A linear regression model will be used, including the baseline rate as an adjusting variable. Moreover, stratified effectiveness analyses will be performed based on baseline audit scores. This approach will enable us to measure the independent effect of the intervention in centers with different levels of potential improvement according to the audit results. All analyses will be conducted on an intention-to-treat basis by a statistician blinded to group allocation, ensuring that participants are analyzed according to their assigned group irrespective of any deviations from the intervention. If necessary, we will handle missing data with multiple imputation. An equivalent methodology will be applied for the secondary outcome variables. All outcome variables (including scores from patient and healthcare professional questionnaires) will be analyzed at the level of healthcare centers (mean score per center). Regarding PREOS-PC scores, we will explore the extent to which the different methods of administration of the questionnaire (face-to-face, telephone, or by email) could yield systematic differences in the scores obtained. In case they do, to minimize a potential confounding bias, we will include the method of administration as an adjustment variable in our regression model. All analyses will be carried out in Stata 14.1 (Stata Corp), using an α of 5% throughout.

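### The safety-action count is scheduled at 24 months only, while the abstract promises, and the analysis needs, a baseline value

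*Protocol article*

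**What the plan says.** Section 2.8.3 (Statistical analysis) gives the model for the primary outcome: "A linear regression model will be used, including the baseline rate as an adjusting variable". It extends that model to the rest: "An equivalent methodology will be applied for the secondary outcome variables". No secondary outcome is exempted.

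Section 2.8.2 lists the action count among the secondary outcomes: "Number of actions aimed at improving patient safety in the center in the last 12 months: An ad hoc questionnaire will be administered". The respondent is each centre's quality and safety referent, in both arms: "including both intervention and control centers, to determine the number of actions taken to enhance patient safety". That section does not say when the questionnaire is given.

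Two other places give the timing:

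- The abstract (Methods) names this count among the secondary outcomes and then states: "Outcome data will be collected at baseline and 24 months follow-up".
- Table 1 (section 2.5.1), in the row "Number of actions aimed at improving patient safety in the center in the last 12 months", reads "Practice level (total number) 24 months follow-up". The other effectiveness rows read "Baseline and 24 months follow-up".

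**The concern.** The analysis text calls for a covariate that the data collection schedule does not provide. A region that works from Table 1 would not ask the question at baseline, and the gap would show only at analysis. By then it could not be repaired cleanly. The respondent would know the centre's allocation (section 2.7 says that professionals cannot be blinded) and would be recalling a period long past. Section 3.1 relies on collecting baseline data before randomization as a protection against bias in an open trial; under Table 1 this is the only effectiveness outcome without a pre-randomization value.

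The outcome is worth measuring well. Increasing the number of safety actions is a named objective (section 1.4), and designing action plans is one of the three elements of the intervention (section 2.2). Section 2.7 also expects centres to differ in safety activity, by region and by teaching status. Differences in prior activity that those two factors do not capture would remain in the residual variance.

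**Working it through.** **Step 1. Effectiveness rows in Table 1, by timing.**

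| Outcome | Baseline | 24 months |
|---|---|---|
| Avoidable hospitalizations (primary) | yes | yes |
| PREOS-PC activation | yes | yes |
| PREOS-PC harm severity | yes | yes |
| PREOS-PC burden of harm | yes | yes |
| PREOS-PC overall safety rating | yes | yes |
| Safety culture (MOSPSC) | yes | yes |
| Adverse events, frequency | yes | yes |
| Adverse events, impact | yes | yes |
| Number of safety actions | **no** | yes |

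Eight of nine rows have a baseline; the action count does not.

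**Step 2. The three statements together.**

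- If Table 1 is right, the abstract is wrong for this outcome, and the baseline term required by section 2.8.3 does not exist for it.
- If the abstract is right, the model can be run, and the Table 1 row is wrong and would mislead those who collect the data.

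Either way, at least one passage needs correcting.

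**Step 3. Is there a substitute?** Table 1 also lists actions registered in the web tool, but only for intervention centres and only during follow-up, so it cannot serve as a baseline. Multiple imputation (section 2.8.3) cannot supply a variable that is absent for every centre.

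**Step 4. The plan's own design figure, for reference.** Section 2.6 gives a difference of 1.5, SD 3.3, one-sided alpha 0.05 and power 80%. Then n per arm = 2 × (1.645 + 0.842)² × (3.3/1.5)² ≈ 59.9, so 60 per arm and 120 in total, against 118 stated. Power with 59 per arm is 0.795. The stated size is reproduced closely. The present point does not rest on it; it only supplies 59 centres per arm for Step 5.

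**Step 5. What a baseline would be worth.** With correlation r between baseline and 24 months, adjustment multiplies the residual variance by 1 − r². The article gives no r for this item; the values below are assumptions.

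- r = 0.3: 1 − 0.09 = 0.91, a 9% reduction; 1/0.91 = 1.10, equivalent to about 10% more centres.
- r = 0.6: 1 − 0.36 = 0.64, a 36% reduction; 1/0.64 = 1.56, equivalent to about 56% more centres.

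The detectable difference in SD units, with 59 per arm and 80% power, is (z for alpha + 0.842) × √(2/59) × √(1 − r²):

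| Assumed r | One-sided 0.05 | Two-sided 0.05 |
|---|---|---|
| 0 (no baseline) | 0.46 | 0.52 |
| 0.3 | 0.44 | 0.49 |
| 0.5 | 0.40 | 0.45 |
| 0.6 | 0.37 | 0.41 |

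At r = 0.6 the factor √0.64 = 0.8 gives 0.458 × 0.8 = 0.37 and 0.516 × 0.8 = 0.41. At r = 0.3 the gain is slight; below 0.3 it is smaller still.

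**The case against.** The strongest reply is that this is a scheduling inconsistency and not a proven defect. The abstract says that a baseline is collected, so the Table 1 row may be a slip. Even if the row is right, section 2.8.3 describes at its core a comparison of arms at 24 months, and an equivalent method need not be an identical one: the baseline term drops out and the rest stands. That much is correct. It does not remove the contradiction, because no exception is written and the table is what a data collector would follow.

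A reader might infer more than the article supports:

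- **That the outcome cannot be analysed.** Only the baseline-adjusted form fails. The unadjusted comparison is unbiased under randomization.
- **That chance imbalance in prior activity could not be dealt with.** Randomization is stratified by region and teaching status, both chosen in section 2.7 for their link with safety activity. Baseline PREOS-PC activation and safety culture are scheduled and could serve as partial proxies.
- **That a linear model is wrong because the count is small.** The article gives no expected count or distribution, and the choice of model for one secondary outcome may properly be left to the analysis plan.
- **That the trial loses the equivalent of 56% more centres.** That is the upper end of an assumed range. A lower correlation is plausible for a single-respondent item measured two years apart, and the trial was not sized on this outcome.

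**Conclusion.** The point holds as an internal inconsistency with a practical consequence. The abstract, Table 1 and section 2.8.3 cannot all be correct for the number of safety improvement actions. Which of them reflects the intention cannot be settled from the article, so it would be wrong to say that the baseline is definitely missing. What can be said is conditional: if Table 1 is followed, the stated adjusted analysis is unavailable for this outcome, and the cost is precision and not validity. The 9% to 36% of residual variance rests wholly on an assumed correlation of 0.3 to 0.6. The primary analysis and the other seven secondary rows are unaffected. The correction deserves to be made because it is cheap and because a clean baseline can be obtained only before allocation.

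**What to change.** Reconcile the three passages in one of two ways.

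1. **If baseline collection is still open:** put the same 12-month question to the safety referent of every centre, with the other baseline questionnaires and before randomization, and change the Table 1 row to baseline and 24 months. The abstract and section 2.8.3 then stand as written. The cost is one question to one respondent per centre, about 118 answers, and one table cell.
2. **If that window has closed:** state in section 2.8.3 that this outcome is compared at 24 months without its own baseline, adjusting for the stratification factors (region and teaching status) and, if wanted, for baseline activation or safety culture scores fixed in advance. Correct the abstract to note the exception. The cost is a sentence in each place and the loss of precision shown above. A baseline recalled after allocation should not be used to fill the gap.

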### Evaluation of the implementation of the SinergiAPS intervention

2.9

Our second objective is to assess the level of success in the implementation of the SinergiAPS intervention and identify contextual factors associated with greater implementation success. This will provide the necessary evidence to design a future large-scale implementation strategy for SinergiAPS. To achieve these goals, we will evaluate each of the five constructs of the Consolidated Framework for Implementation Research (CFIR) model (44): the intervention itself, the inner setting, the outer setting, the individuals involved, and the processes by which the intervention implementation is achieved.

#### Data collection

2.9.1

In-depth qualitative interviews with professionals from the intervention group (approximately 30 qualitative interviews, until reaching saturation of discourse). These interviews aim to examine the overall assessment of the SinergiAPS intervention, identify aspects for improvement, and gather suggestions to facilitate the large-scale implementation of the intervention. Sampling will be intentional, including informants of both genders, different age groups, professional categories, and territorial areas.Quantitative interviews: Through an online questionnaire administered quarterly to the project referent in each center, we will measure the usability of the intervention, as well as the degree of use, acceptability, and perceived usefulness.Level of usage of the SinergiAPS web tool: We will examine the extent of the tool’s utilization by monitoring the number of accesses made by healthcare centers. We will determine whether the healthcare centers have accessed the feedback report or not. Additionally, we will determine the frequency of accesses and usage time of the module within the tool that provides training and support materials for designing and implementing action plans.Analysis of the action plans proposed by the healthcare centers: The web tool includes a module aimed at systematically recording the action plans formulated by healthcare centers. This comprehensive repository of information remains securely registered within the tool and provides valuable insights for examining the implementation of the intervention.Implementation diary: In each node, the researchers will maintain an active record of the barriers encountered during the implementation process of the intervention in the centers.

#### Data analysis

2.9.2

We will analyze the quantitative data (quantitative interviews and level of usage of the SinergiaAPS tool) using descriptive statistics at the center level (e.g., mean and standard deviation of usability and perceived utility scores). We will conduct a trend analysis to monitor the levels of usage over time, every 3 months.

We will analyze the qualitative data from the in-depth qualitative interviews with professionals using thematic analysis (45). For the analysis of the action plans proposed by the healthcare centers, and of the implementation diary, we will use content analysis (46). Both types of analysis will be conducted independently by two experienced researchers. Discrepancies will be discussed with the research team until an agreement is reached concerning the list of themes and codes. We will use NVivo 14 to support the analysis of the qualitative data.

### Trial management

2.10

The main coordinating center will be at the Primary Care Research Unit of Mallorca—the Balearic Islands Health Research Institute (IdISBa). A trial coordinator from each participant region will contact PHC center coordinators to manage recruitment, trial initiation, and implementation of the intervention as well as for the qualitative data collection for the process evaluation. They will also be responsible for collecting the data from the included centers, professionals and patients. Patient and professional identifiable data will be accessible only to the researchers from the same region. We will generate a database with no identifiable information, which will be accessed by the trial analyst (blinded to group allocation) through a password-protected portal. Data from implementation analysis will also be kept in a password-protected portal.

Trial modifications will undergo review by the Ethics Committee for approval, will be documented in our registered protocol, and will be included in the final manuscripts.

## Discussion

3

The proposed study has the potential to have an impact on clinical practice, healthcare systems, and population health. In terms of clinical practice, this study will provide the evidence-based tool, SinergiAPS, which enables PHC centers in Spain to systematically collect patients’ perceptions and experiences concerning the safety of their care. Moreover, it will offer a structured approach for the centers to receive and integrate this information with other patient safety intelligence, enabling the development of patient-centered action plans for specific improvements. In terms of impact on the healthcare system, the proposed SinergiAPS intervention has been designed to minimize costs while maximizing scalability and sustainability. By utilizing a dedicated web-based tool for collecting patient experiences and automatically generating customized feedback reports, it can be widely implemented in PHC centers with limited external support and at a low cost. As such, this intervention has the potential to be a cost-effective, feasible, and sustainable strategy for enhancing patient safety in the PHC setting. If effective, it could contribute to reducing the estimated annual costs associated with safety incidents in PHC [around 2.5% of total healthcare spending (7)].

In terms of impact on population health, it is worth noting that experiencing errors in the PHC settings can lead to severe harm and even death. Notably, a recent OECD report highlights adverse events as the cause of over 7 million avoidable hospitalizations each year (7). Such incidents also result in emotional distress for patients and healthcare professionals, with the latter considered second victims of adverse events. The widespread implementation of the SinergiAPS tool in PHC centers have the potential to play a significant role in preventing harm, reducing avoidable hospitalizations, and improving population health. Notably, patient safety issues in PHC disproportionately affect socially vulnerable groups, such as women and individuals with lower educational levels, as evidenced by recent research (47). Therefore, if SinergiAPS proves effective, it could contribute to reducing health inequalities.

### Strengths and limitations of the proposed study

3.1

This study represents the first large-scale trial to evaluate an intervention to improve patient safety in PHC centers through the integration of patient-reported safety experiences and outcomes. By involving a significant number of centers, this research aims to comprehensively assess the impact of the intervention over a 24-month follow-up period, using a combination of consolidated administrative data, such as avoidable hospital admissions, as well as validated questionnaires like PREOS-PC and MOSPSC. The evaluation of the implementation of SinergiAPS will be guided by CFIR, a well-established and widely recognized framework. By adopting CFIR, we will be able to holistically examine the factors influencing the implementation process, considering both internal and external elements that may affect the intervention’s success. All these are novel aspects that make our study unique in terms of study design and approach.

The study also has some limitations that warrant consideration. Firstly, being a multicenter project with researchers from several regions in Spain and a comprehensive network of national collaborators, recruiting centers from all regions may pose challenges. Nevertheless, this would have a minimal effect on the overall number of healthcare centers to be recruited, which remains manageable within the participating nodes. Although this limitation is not expected to significantly impact the external validity of the study, the exclusion of centers from specific regions could restrict the evaluation of SinergiAPS implementation due to the unique characteristics of regional healthcare systems. Secondly, intentional sampling of healthcare centers has been chosen as the preferred sampling method, as random sampling is not feasible and could introduce potential selection bias. Thirdly, patient safety research in PHC is still in its early stages, and the lack of established “gold standard” measures for evaluating patient safety could constrain the comprehensive assessment of SinergiAPS’s effectiveness. However, the proposed outcome variables collectively encompass a wide range of aspects related to patient safety in PHC, allowing for evaluation from multiple perspectives. Lastly, due to the nature of the intervention, blinding of healthcare centers is not possible. However, randomization will be conducted after baseline data collection, and efforts will be made to maintain blinding among analysts to minimize bias. It will be crucial to address this potential source of bias in the analysis and interpretation of the study results.

